### Sample size

As there are no data on the effect of rivastigmine treatment on step time variability, our sample size calculation has been estimated by extrapolating from related studies. For example, it has been found that treatment with donepezil resulted in a reduction in gait variability (22.3 to 11.3% CoV) for AD patients in a non-randomized trial [25].

Pragmatically, we estimate that we can recruit 130 eligible participants for the study over a 12 month period. Assuming a 30% drop out (based on a previous RCT [45]) this would result in approximately 90 patients (45 per arm) with trial data. This will enable us to detect a treatment effect difference of 0.6 standardised (z-score) units for our primary outcome measure (step time variability) with 80% power and at a two-sided 5% significance level. This sample size is similar to a study currently being undertaken in non-PD patients with mild cognitive impairment, i.e. 140 participants [28]. The use of a dual-task paradigm, as a cognitive stressor, may produce a more sensitive measure of any treatment benefit.

The clinical impact of such a group difference in gait variability can be estimated from a study by Maki [52]. In a cohort of 75 elderly volunteers without PD, a 0.6 standardised difference in stride velocity and stride length was associated with a 1.65 and 1.50 increased odds ratio of falling respectively, which would translate into clinically important benefits. We have assumed that these results will generalize to PD populations, and also manifest in step time variability, possibly a better predictor of fall risk in this population [53].

### Statistical analysis

Simple descriptive statistical analyses will initially be undertaken on all outcomes measures. For continuous measures (e.g. step time, step length and variability) the mean, SDs and distributions will be examined. Where measures are skewed, transformation will be undertaken. Outcome data on falls will be analysed by: (i) number of falls (count), (ii) non-fallers, low frequency of falls and frequent fallers (categorical ordinal variable), (iii) fall rate per person month (rate) and (iv) proportion of fallers in each group. Injury data will be summarized as (i) peripheral fracture rate per person-year of follow-up, (ii) number of peripheral fractures, (iii) number of people sustaining peripheral fractures, and (iv) number of people sustaining multiple events. For these variables, frequency counts (e.g. categorical variables) or Kaplan Meier plots for survival time variables will be analysed. Other binary or categorical measures (such as adverse event data) will be examined by simple frequency counts and contingency tables with Chi^2^ tests of association.

The main analyses will be performed using the intention to treat principle. For the primary outcome measure (step variability), we will use multivariable linear regression models and adjust for baseline or other covariates to increase precision. Hence we will compare group differences at 32 weeks in the gait variability parameters conditional on baseline parameters. For the secondary outcomes we can use ordinal logistic regression (e.g. for frequency of falls as an ordinal variable), Cox’s proportional hazard model for time to first fall and negative binomial regression to compare fall rates between groups. The last method accounts for falls clustering within participants, and has been recommended for falls data analysis [54]. The baseline covariates will be adjusted for as appropriate.

For participants who fail to complete the follow-up, sensitivity analyses will be undertaken, using multiple imputation methods. There are no planned interim analyses and no formal adjustments will be used for multiple testing though we will be cautious in our interpretation of the secondary outcomes (especially when the p-value is in the range of between 0.01 and 0.05) given the possibility of type I errors.

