### Primary outcome measure - step time variability

The primary outcome measure will be step time variability assessed in three walking conditions: normal walking, (b) walking while performing a verbal fluency task and (c) walking while performing a verbal fluency switching task. Variability will be calculated according to current recommendations [47] as both the standard deviation (SD) and the coefficient of variation (CoV) (SD/mean x 100%). The SD for the three walking conditions will be reported as the primary outcome measure, though we hypothesise a priori that any observed differences will be magnified with increasing cognitive demands. Each condition is repeated three times for a total of nine walks. Gait will be assessed with an accelerometer, housed in a small, lightweight (5 g) container attached to the participant’s waist with an elasticated belt (Dynaport Hybrid system, McRoberts). Participants will be tested whilst in the ‘on’ medication state and will be instructed to walk at self-selected speeds over a 22 m obstacle-free level corridor, wearing their normal footwear and clothing. During the dual-task conditions, participants will not be given instructions as to which task to prioritise. The verbal fluency task is based on the controlled oral word association test (COWAT) whereby participants are asked to name as many words as they can beginning with a given letter of the alphabet. The switching dual-task is a more challenging version of COWAT. Participants are instructed to switch alternately between words beginning with two different letters of the alphabet. Letters are selected based on their frequency in the English dictionary and thus perceived difficulty. The three walking conditions will be randomly ordered to minimise practice effects. In the event of a failure on either the cognitive task or walking the participant will be prompted to continue. Cognitive task performance will be recorded using a lightweight non-obstructive dictaphone worn by participants.

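### Three step time SDs share the primary outcome with no lead condition or success rule, so the stated 5% level and 80% power cannot both be relied on.

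*Protocol article*

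**What the plan says.** The section on the primary outcome measure opens with "The primary outcome measure will be step time variability assessed in three walking conditions" and adds "The SD for the three walking conditions will be reported as the primary outcome measure". CoV is also calculated, but SD is the version named as primary, so there are three primary measures, not six. The same section states an expectation: "we hypothesise a priori that any observed differences will be magnified with increasing cognitive demands".

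For the analysis, the Statistical analysis section says "we will use multivariable linear regression models and adjust for baseline or other covariates to increase precision" and then "we will compare group differences at 32 weeks in the gait variability parameters conditional on baseline parameters". Both models and parameters are in the plural. On multiplicity it says "no formal adjustments will be used for multiple testing though we will be cautious in our interpretation of the secondary outcomes". No interim analysis is planned, so no other use of alpha is in play.

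The Sample size section expects 130 recruits, 30% dropout and about 45 per arm with data, giving a detectable difference of 0.6 standardised units "with 80% power and at a two-sided 5% significance level". That is a calculation for one comparison.

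**The concern.** The three sections do not fit together. The outcome has three components, the power statement has one, and the multiplicity statement declines adjustment while confining caution to secondary outcomes. Nothing says how three results become one conclusion.

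What is at stake is the meaning of a positive trial. Suppose the switching task gives p = 0.03 and the other two conditions are not significant. The article does not say whether the primary outcome has been met. The answer could then be chosen after the data are seen, and the error rate and power that apply would depend on that choice.

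**Working it through.** **Inputs.** From the Sample size section: 45 per arm, difference 0.6 SD, two-sided 5%, 80% power. From the primary outcome section: three conditions. The correlation r between the three test statistics is not in the document. It is an assumption, taken as equal for each pair and shown over a range.

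**1. The plan's own figure.** 130 × 0.7 = 91, about 45 per arm. A two-sample t-test with 45 per arm and 0.6 SD at two-sided 5% has 80.4% power (81.2% by the normal approximation), and the detectable difference at 80% power is 0.597 SD. The stated calculation is correct for a single comparison.

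**2. Any one of three counts as success.** For independent tests, the chance of at least one false positive is 1 − 0.95³ = 14.3%. For correlated tests it comes from simulating three normal statistics with no treatment effect and counting how often at least one exceeds 1.96 in absolute value. The last column counts only statistics beyond 1.96 in the direction of benefit.

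| r | At least one false positive | In the direction of benefit |
|---|---|---|
| 0 | 14.3% | 7.3% |
| 0.5 | 12.5% | 6.3% |
| 0.7 | 10.9% | 5.4% |
| 0.8 | 9.8% | 4.9% |
| 0.9 | 8.4% | 4.2% |

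The reference for one test is 5% in the first column and 2.5% in the second. The first column stays above 5% for every r below 1.

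**3. All three must succeed.** With no effect in any condition, the error is 0.01% at r = 0 and 2.3% at r = 0.9. It cannot exceed 5%, because each test is itself held at 5%. Power with 0.6 SD in every condition is the chance that all three statistics exceed the critical value. Each statistic has mean 0.6 / √(2/45) = 4.74 × 0.6 = 2.85. Simulation gives about 62% to 63% at r = 0.5, 69% to 70% at r = 0.8 and 72% to 74% at r = 0.9 (lower figure from the t-test, upper from the normal approximation). All are below 80%.

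**4. Bonferroni, for comparison.** At 0.05/3 = 0.0167 per condition, power for 0.6 SD with 45 per arm is 65.7% and the detectable difference is 0.69 SD. Restoring 80% power needs 60 per arm, so 120/0.7 ≈ 172 recruited against the 130 planned.

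**5. One averaged contrast.** The mean of three equally variable, equally correlated measures has SD √((1 + 2r)/3) in units of one condition's SD. With 0.6 SD in each condition:

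- r = 0.5: SD 0.816, effect 0.6/0.816 = 0.735, power 93%
- r = 0.7: SD 0.894, effect 0.671, power 88%
- r = 0.9: SD 0.966, effect 0.621, power 83%

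If the effect is confined to one condition, the average is 0.6/3 = 0.2. At r = 0.7 the standardised effect is then 0.2/0.894 = 0.22, and power is about 18%.

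**6. Fixed sequence.** The first test is one comparison at 5%, so its power is that of step 1 if the standardised effect there is 0.6. The overall error is 5%, because later tests are reached only after earlier ones succeed.

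**The case against.** A reader might infer that each condition is tested separately, that any one success makes the trial positive, and hence that the 5% level is simply broken. The article does not say this. Separate tests are the natural reading of the plural models and parameters, but the success rule is an inference, and 5% still holds for each test taken alone. Nor can the inflation be put flatly at two to three times. That depends on a correlation the document does not give: at r = 0.9 it is 8.4/5, about 1.7 times, and independence is implausible for one measure taken on the same person, with the same sensor, in one session. These objections stand.

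An unseen analysis plan could name a lead condition or one averaged contrast without contradicting the refusal to adjust. That is fair, but it does not repair the article, which settles the multiplicity question and restricts its caution to secondary outcomes. What decides the trial is ordinarily a protocol matter.

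The prior expectation about cognitive demand limits free choice somewhat: an isolated effect in normal walking would contradict it. It predicts a pattern of effects, however, and sets no testing order.

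Finally, this is a single-centre phase II trial of pragmatic size, and all three SDs are to be reported. That lessens the consequence and the room for selective reporting. It does not say which result decides.

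**Conclusion.** The point holds in this form: the protocol fixes three primary measures and declines adjustment, but does not fix the rule that turns them into one conclusion. Under an any-of-three rule, the false positive chance is about 8% to 14% (r from 0.9 to 0), about half of it towards benefit. Under an all-three rule, error is controlled but power is about 62% to 73% (r from 0.5 to 0.9). Neither gives two-sided 5% and 80% power together.

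These figures assume equal pairwise correlations, 45 evaluable per arm and, for power, 0.6 SD in every condition. Like the plan's own calculation, they take no credit for baseline adjustment. The sample size arithmetic itself is sound.

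**What to change.** Before unblinding, state one primary test in the protocol or analysis plan. Either of these keeps 5% overall:

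- **Averaged contrast.** Fit one repeated-measures model of the three SDs, adjusted for baseline, with the treatment effect averaged over conditions as the single primary contrast. Power is about 83% to 93% (r from 0.9 to 0.5) if the effect is 0.6 SD in each condition. The cost is that an effect confined to one condition is diluted.
- **Fixed sequence.** Test at 5% each, first the switching task, then verbal fluency, then normal walking, and stop at the first non-significant result. This follows the protocol's own expectation. Power for the first test is about 80% only if the standardised effect there is 0.6. The protocol expects a larger difference under greater demand, but if the spread between participants also rises, the standardised effect need not be larger. The cost is that later conditions can be claimed only if earlier ones succeed.

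In both cases, report all three condition-specific effects with confidence intervals. The change is to wording only, with no new data and no additional participants.

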**Methods/design:**

This is a single centre, double-blind, randomised placebo-controlled trial in 130 people with Hoehn and Yahr stage 2–3 idiopathic Parkinson’s disease who have fallen in the past year. Participants will be randomised to two groups, receiving either rivastigmine capsules or identical placebo capsules for 8 months. Assessment will be undertaken at baseline and at the end of medication prescription (i.e. 8 months) with participants remaining enrolled in the trial for a further 4 months to monitor for falls and adverse events. The primary outcome is step time variability, assessed with and without the addition of concurrent cognitive tasks. Secondary outcomes will include other gait parameters, sensorimotor and balance performances, cognitive indices, falls and fall related injury, fear of falling, Parkinson’s symptoms and data pertaining to possible harms.

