**Falls, resultant injuries and adverse events**			
Falls, injuries and use of medical services will be collected by monthly phone calls and diaries.	✓	✓	2°
Adverse events will be screened for during monthly follow-up phone calls	✓	✓	2°

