#### Safety

Participants will be asked to notify the research team by phone if they experience any adverse events. Additionally, all participants will be screened during the monthly phone calls for adverse events using an open ended, non-leading question. Serious adverse events will be defined as events that result in death, hospitalisation (except for a pre-existing condition that had not worsened), significant disability or incapacity.

Potential worsening of extrapyramidal symptoms has been previously cited as a concern when prescribing cholinesterase inhibitors in Parkinson’s disease. A large multicentre placebo controlled trial of 541 people with mild to moderate dementia related to Parkinson’s disease demonstrated improvement in cognitive scores [45]. Worsening of tremor is a recognised side effect of rivastigmine but was only sufficiently severe to cause withdrawal of 1.7% of patients treated in the aforementioned trial. Monthly phone calls and access to the trial team should facilitate rapid reporting of such symptoms and appropriate down titration or cessation of the drug where clinically appropriate.

Adherence will be measured with a pill count of returned medications. This will be compared with the participant’s reported adherence on the basis of information ascertained during the follow-up phone calls and at the second face-to-face assessment visit.

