## Discussion

Falls and the consequences thereof are devastating to people with Parkinson’s disease. This trial will provide new insight into the effect of cholinesterase inhibitors on gait, balance and fall risk in this vulnerable group. It will establish and further validate falls prediction algorithms and delineate the interaction of multiple key risk factors that contribute to the high rate of falls that occur in this vulnerable population. Rivastigmine could potentially represent a safe and cost effective therapeutic approach to treating gait and balance dysfunction in Parkinson’s disease utilising an already established pharmacological agent. Hence, this may offer an effective, acceptable intervention in an area of Parkinson’s disease where there are currently unmet symptom needs and little in the way of evidence based therapeutic strategies.

## Appendix 1

The gait parameter definitions are described in Table 2. Step time variability is the primary outcome measure. The effect of the intervention will be measured on the other gait parameters listed.

**Table 2 T2:** Gait parameter definitions used in the ReSPonD trial

**Gait parameter**	**Definition**
Stride	One stride equals two steps and represents one gait cycle.
Stride time	Time taken for one stride
Stride length	Distance traversed by two steps
Step	Defined by consecutive heels strikes of contralateral limbs
Step time	Time taken for one step
Step length	Distance between consecutive heel strikes, mean is calculated by the distance travelled / number of steps taken.
Walking speed	The velocity of walking, calculated as the distance travelled / time taken.
Variability	Variability of the measure of interest, expressed as the standard deviation (SD) and the coefficient of variation (CoV) = SD/mean x 100%.
Double limb support	The period for which both feet are in contact with the floor, calculated by time from heel strike until toe off of the contralateral limb.
Cadence (steps/min),	The number of steps per minute
Stance time (sec)	Duration of stance time (single and double support) in one gait cycle.
Walk ratio	The relationship between the amplitude and frequency of the rhythmic leg movements when walking. Calculated as step length / cadence.

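### The type I error caution on secondary outcomes also covers adverse events, where it points the wrong way; limit it to efficacy and report harms as risk differences with confidence intervals

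*Protocol article*

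**What the plan says.** Table 1 of the protocol article, under falls, injuries and adverse events, has the row "Adverse events will be screened for during monthly follow-up phone calls" and marks it as a secondary outcome. The Methods/design part of the abstract ends its list of secondary outcomes with "fear of falling, Parkinson’s symptoms and data pertaining to possible harms".

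The Statistical analysis section gives one method for comparing adverse events between arms: "Other binary or categorical measures (such as adverse event data) will be examined by simple frequency counts and contingency tables with Chi^2^ tests of association". In its last paragraph the section makes no multiplicity adjustment and adds: "we will be cautious in our interpretation of the secondary outcomes (especially when the p-value is in the range of between 0.01 and 0.05". The stated reason is "given the possibility of type I errors". The sentence covers the secondary outcomes as a whole. It does not exempt adverse events or serious adverse events, and type II error is not mentioned.

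The Safety section names the harm of most interest: "Potential worsening of extrapyramidal symptoms has been previously cited as a concern when prescribing cholinesterase inhibitors in Parkinson’s disease". Parkinson's disease severity on the MDS-UPDRS is also a secondary outcome in Table 1, so the same caution applies to it.

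**The concern.** Caution about false positives protects patients when the claim is benefit. When the claim is harm, it asks for stronger evidence before a signal is believed. The sample size rests on the gait outcome alone, so for most adverse events the trial has limited power, and the more likely error is to overlook a real excess. A rule that adds scepticism to the signals that do appear, in the range where moderate harms often land, adds to that error.

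At stake is how the safety results are read. An excess of adverse events on rivastigmine with p between 0.01 and 0.05 could be given too little weight, and the p-value says nothing about how large a harm remains compatible with the data.

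**Working it through.** **1. The plan's own figure.** Inputs from the Sample size section: 0.6 SD, 80% power, two-sided 5%, 130 recruited, 30% drop-out, about 45 per arm analysed.

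- n per arm = 2 × (1.960 + 0.842)² / 0.6² = 43.6, so 44.
- Power at 45 per arm is 80.4% (noncentral t).
- 130 × 0.7 = 91.

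The stated figure holds. It concerns step time variability only.

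**2. Power for harms.** Adverse event rates per arm are an assumption, because the article gives none. All 130 randomised, with equal allocation, gives 65 per arm. The method is exact binomial enumeration of every pair of counts (a on placebo, b on rivastigmine), with the uncorrected Pearson statistic

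X² = (a/n − b/n)² / [p̄(1 − p̄)(2/n)], where p̄ = (a + b)/(2n),

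counting only results with more events on rivastigmine.

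| True rates, placebo v rivastigmine | p<0.05 | p<0.01 | p from 0.01 to 0.05 |
|---|---|---|---|
| 5% v 10% | 19% | 6% | 13% |
| 10% v 20% | 35% | 15% | 20% |
| 5% v 15% | 49% | 24% | 25% |
| 10% v 25% | 62% | 37% | 25% |
| 10% v 30% | 83% | 62% | 21% |
| 10% v 40% | 99% | 94% | 5% |

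With 45 per arm, 10% v 20% gives 28%, 9% and 19%, and 10% v 30% gives 69%, 42% and 27%.

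**3. What comes from where.** At 10% v 20%, 65% of trials miss p<0.05 because of sample size alone. The band adds 20 points of results that would be read with special caution. Over the rows shown, the band holds 5% to 25% of trials.

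**4. One example.** Take 15/65 on rivastigmine and 6/65 on placebo.

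- Risk difference = 0.231 − 0.092 = 0.138.
- Standard error = √(0.231 × 0.769/65 + 0.092 × 0.908/65) = 0.063.
- Wald 95% CI = 0.138 ± 1.96 × 0.063, or 1.4 to 26.3 percentage points.
- Chi-squared p = 0.032 uncorrected and about 0.057 with continuity correction.

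The article does not say which version applies, so the same data sit inside the caution band or above 0.05 according to that choice. The estimate of about 14 points does not depend on it.

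**5. The converse.** If both arms show 10%, the 95% CI half-width is 1.96 × √(2 × 0.1 × 0.9/65) = 0.103. A result with no difference at all is still compatible with an excess of about 10 points.

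**6. Sparse events.** The only harm rate in the article is 1.7% withdrawal for tremor among treated patients in an earlier trial. That is 65 × 0.017 = 1.1 expected participants. With no placebo events, uncorrected p<0.05 needs 4 v 0, which has a 2.5% chance. A chi-squared test is poorly suited to tables of this kind.

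**The case against.** The strongest reply is that the plan says only that the authors will be cautious. It does not say that results with p from 0.01 to 0.05 will be set aside, and it sets no 0.01 threshold. That stands. The p<0.01 column above shows where results fall; it is not the operating characteristic of a rule in the plan.

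A reader might also infer that harms rest on significance tests alone. They do not. Frequency counts are planned, falls have their own models, and the MDS-UPDRS is measured at both visits. Monthly screening and the handling of individual side effects do not depend on a p-value.

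A third tempting reading is that the plan treats non-significance as proof of safety. No sentence says so. The Discussion's "Rivastigmine could potentially represent a safe and cost effective therapeutic approach to treating gait and balance dysfunction" is a conditional hope and not an analysis rule.

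Two further points have weight. Open-ended monthly questioning yields many event types, so chance imbalances are a genuine concern. Intervals and exact methods could also be left to a fuller document. But the chi-squared test and the unqualified caution are stated here, and the point concerns that stated text. Concern about many event types supports labelling the comparisons as descriptive. It does not support a caution that also covers serious events without distinction.

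**Conclusion.** The point holds in a limited form. Adverse events are secondary, their only stated between-arm test is chi-squared, and the type I caution reaches them without exemption. For harms that is the wrong direction of caution.

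Under assumed rates of 10% v 20%, 5% v 15% and 10% v 25% with 65 per arm, 35%, 49% and 62% of trials reach p<0.05, and 20% to 25% fall in the caution band. Moderate harms may therefore be missed or under-weighted. The documents do not support saying that harms in general are likely to be missed. Sample size causes most of the misses, no change of wording alters that, and at 10% v 40% the test succeeds in 99% of trials. The figures rest on the assumed rates, equal allocation, all randomised participants being counted, and the uncorrected test. This is a cheap improvement to stated text and leaves the primary analysis untouched.

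**What to change.** In the Statistical analysis section:

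1. Limit the type I error caution to secondary efficacy outcomes, and state that it does not apply to adverse events or serious adverse events.
2. Replace the chi-squared test for adverse events with the number of participants affected per arm and the risk difference with 95% CI, reported whatever the p-value, using exact or score methods where events are sparse. Base any safety statement on the interval and not on non-significance.
3. Report the MDS-UPDRS as an estimate with 95% CI, read the same way for improvement and for worsening. Exempting worsening alone would treat one two-sided comparison asymmetrically.

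The cost is two or three sentences and intervals computed from data already collected, with no extra participants or procedures. The downside is that, with many event types, some chance imbalances will be shown at face value. They should be labelled descriptive.
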